### Sample Size

This study proposes to enroll 80 ADRD family caregivers, randomized in equal numbers (n=40 per group) to either the intervention or attention control conditions. Consistent with stages 0-1B of the National Institutes of Health (NIH) stage model for behavioral intervention development [46], the primary goal of this pilot study is to establish the feasibility and acceptability of CarePair. Accordingly, the study is not powered to detect clinically meaningful differences in outcomes. A sample size of 40 participants per arm exceeds the upper limit recommended (n=35) for feasibility trials [43] and allows for adequate precision in estimating key feasibility parameters (recruitment, retention/attrition, and platform usability), which will inform prespecified progression (go/no-go) criteria for advancing to a full-scale RCT. This approach is consistent with methodological guidance for pilot and feasibility studies, which prioritizes the estimation of feasibility parameters over formal hypothesis testing or power-based sample size calculations [47-50]. Preliminary efficacy will be explored as a secondary aim to estimate effect sizes and associated CIs to guide the design of a subsequent, fully powered efficacy trial.

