### Randomization Process

After providing consent and completing the baseline survey, participants will be randomized to either the intervention or attention control group using REDCap’s randomization module. A stratified permuted block randomized design is utilized to enhance internal validity and minimize potential confounding variables. Randomization tables are generated by an RA, who is not involved in data collection or participant randomization, using a custom Python script.

To ensure demographic balance across study arms while accommodating the target sample size (n=80), randomization is stratified based on caregiver sex and race/ethnicity, resulting in 24 unique strata. Within each stratum, 25 permuted blocks of 4 are created, each containing 2 “intervention” and 2 “control” assignments, randomly shuffled using Python’s random shuffle() function to ensure unpredictability. The full table is compiled into a .csv file and uploaded to REDCap’s secure randomization module. Once uploaded, the allocation table is locked and inaccessible (ie, no longer visible or modifiable) to study staff. Participants will be randomized in real time via REDCap after stratification variables are entered (sex and race) to preserve allocation concealment and ensure balanced/methodologically sound group assignment. Once randomized, study staff are unable to change participants’ group assignments.

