### Statistical Analysis

Descriptive statistics (eg, frequencies, means, and SDs) will be used to characterize the study sample across arms. The intervention’s feasibility and acceptability will be evaluated through recruitment and retention rates, reasons for noncompletion, app usage data (eg, number of log-ins and in-app actions), and participant usability and satisfaction assessments. Independent samples *t* tests for continuous variables and chi-square tests for categorical variables will be used to test for baseline group differences in sociodemographic characteristics and primary and secondary outcome measures (eg, stress and self-efficacy). Relationships among continuous measures will be examined using Pearson correlations. Additional analyses will examine the relationships between covariates (eg, age, education, and kinship), and outcome measures will be examined for inclusion in multivariate models.

To examine preliminary efficacy, within- and between-group differences in secondary outcomes will be assessed. Specifically, we will examine (1) mean values at each time point by group, (2) within-group change from baseline to follow-up, (3) between-group differences in change, and (4) standardized effect sizes (eg, Hedges g) with 95% CIs to guide planning for a future efficacy trial. Missing data will be handled via listwise deletion. A *P *value of .05 will be used to indicate significance in all analyses.

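### Efficacy is estimated from the between-arm difference in change, with baseline significance tests and covariates screened on the trial data; a prespecified baseline-adjusted ANCOVA would be more precise at almost no cost

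*Protocol article*

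**What the plan says.** All of the following is in the protocol article.

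- **Estimator (Statistical Analysis).** Preliminary efficacy is read from group means at each time point, then "2) within-group change from baseline to follow-up", then "3) between-group differences in change, and (4) standardized effect sizes (eg, Hedges g) with 95% CIs". The stated purpose of the effect sizes is to plan a future efficacy trial. No model with the baseline score as a covariate is named.
- **Baseline tests (same section).** t tests and chi-square tests "will be used to test for baseline group differences in sociodemographic characteristics and primary and secondary outcome measures". The examples given there, stress and self-efficacy, are both secondary outcomes.
- **Covariates (same section).** Age, education and kinship are named as example covariates, and "outcome measures will be examined for inclusion in multivariate models". The sentence is garbled, but its natural reading is that covariate-outcome relationships in the trial data decide which covariates enter.
- **Randomisation (Randomization Process).** "randomization is stratified based on caregiver sex and race/ethnicity, resulting in 24 unique strata". Neither factor is named as an adjustment term.
- **Size (Sample Size).** 80 caregivers, "randomized in equal numbers (n=40 per group"), and "the study is not powered to detect clinically meaningful differences in outcomes".
- **Timing of measures (Table 1 and the outcome sections).** The six secondary outcomes described in the text (needs, self-efficacy, anxiety, depression, stress, quality of life) are all measured at baseline and at 6 weeks. The primary usability and acceptability measures are collected at follow-up only.

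**The concern.** Subtracting the baseline score fixes its coefficient at 1, whereas ANCOVA estimates it from the data. With equal SDs at the two visits, the best coefficient is rho, which is below 1 for any imperfectly correlated outcome, so the change score carries avoidable noise. In a trial of this size the intervals are already wide, and they are intended to feed the next sample size calculation.

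Two steps around the estimator add nothing useful. A significance test of baseline balance checks a null hypothesis that randomisation makes true, and for the follow-up-only primary measures there are no baseline data to test. Choosing covariates from their observed relation to the outcome, with an open-ended list and no stated rule, lets the adjusted estimate depend on decisions taken once the data are in hand. The trial is unblinded, so fixing those decisions beforehand is worth something.

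**Working it through.** The plan gives no power or precision figure to reproduce; 40 per arm comes from a feasibility rule.

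**Inputs**
- 40 randomised per arm (Sample Size).
- Attrition of 15% to 30% is cited as common in pilots (Retention and Adherence), and missing data are deleted listwise (Statistical Analysis). Completers per arm: 40 × 0.85 = 34, or 40 × 0.70 = 28.
- Assumptions: equal SDs at baseline and follow-up, and rho from 0.3 to 0.8. The article gives no rho.

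**Variance per participant, in units of SD²**
- Change score: 2(1−rho).
- ANCOVA: 1−rho².
- Ratio of ANCOVA to change: (1−rho²) / [2(1−rho)] = (1+rho)/2.

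**95% CI half-width for the arm difference, in outcome SDs, n completers per arm**
- Change: t(2n−2) × √[2(1−rho) × 2/n].
- ANCOVA on baseline: t(2n−3) × √[(1−rho²) × (2/n) × (1 + 1/(2n−4))]. The last factor is the small-sample cost of fitting the baseline slope.

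Worked case, n = 34 and rho = 0.5: change 1.997 × √(1.00 × 2/34) = 0.484; ANCOVA 1.997 × √(0.75 × 2/34 × 65/64) = 0.423.

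| rho | variance ratio | change, n=34 | ANCOVA, n=34 |
|---|---|---|---|
| 0.3 | 0.65 | 0.573 | 0.466 |
| 0.5 | 0.75 | 0.484 | 0.423 |
| 0.7 | 0.85 | 0.375 | 0.349 |
| 0.8 | 0.90 | 0.306 | 0.293 |

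At rho 0.5 the same comparison is 0.445 against 0.388 with 40 per arm, and 0.536 against 0.469 with 28. Below rho 0.5 the change score is noisier even than the follow-up score alone (variance 1.4 against 1.0 at rho 0.3).

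**Adding the randomisation factors.** With k further terms that predict nothing, the degrees of freedom become 2n−3−k and the last factor becomes 1 + (k+1)/(2n−4−k). The article does not list the factor levels, so k is assumed. With n = 34:

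| rho | change | k=0 | k=4 (collapsed) | k=9 to 12 (uncollapsed) |
|---|---|---|---|---|
| 0.5 | 0.484 | 0.423 | 0.437 | 0.457 to 0.471 |
| 0.7 | 0.375 | 0.349 | 0.360 | 0.377 to 0.388 |

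The gain therefore comes from the baseline score. Uncollapsed and non-prognostic, the stratification terms can use it up. With 80/24 = 3.3 people per stratum, the strata themselves cannot be fitted sensibly.

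**Baseline tests.** 7 sociodemographic items (Table 1) + 6 secondary outcomes = 13 tests. Expected false positives: 13 × 0.05 = 0.65. Chance of at least one, if independent: 1 − 0.95¹³ = 49%.

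**Covariate screening.** A null simulation (3,000 runs, 34 per arm, 7 candidate covariates, rho 0.5 and 0.7) gave a type I error of 0.051 to 0.052 for one change-score model with covariates chosen by their correlation with the outcome. It rose to about 0.068 when the best of three analyses could be reported: unadjusted, outcome-selected and imbalance-selected.

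**Standardiser.** The article does not say which SD divides the difference. Dividing by the change SD instead of the raw SD multiplies g by 1/√[2(1−rho)]: 0.85 at rho 0.3, 1.00 at 0.5, 1.29 at 0.7 and 1.58 at 0.8.

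**The case against.** The strongest reply is that a difference in change is a valid estimator, that this is an unpowered feasibility pilot in which efficacy is secondary, and that model detail belongs in an analysis plan that is not shown. Much of that stands. The preference for ANCOVA is an efficiency recommendation, and the unspecified multivariate models might include the baseline score. But the article does state its estimator, its baseline tests and its screening step, so these are choices open to comment and not details merely left out.

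Several stronger readings are tempting, and the documents do not support them:

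- *That the change estimate is biased, or that chance baseline imbalance is a separate harm.* Under randomisation the estimator is unbiased on average. Its sensitivity to imbalance is the same variance loss already counted in the half-widths.
- *That the baseline tests choose the covariates.* The text puts the two steps near each other but does not connect them.
- *That every scale in Table 1 is tested at baseline.* The section limits the tests to sociodemographic characteristics and primary and secondary outcomes, hence about 13.
- *That omitting the stratification factors makes the intervals materially too wide.* This holds only if sex and race/ethnicity predict the outcomes, which nothing in the article shows.
- *That covariate screening seriously inflates type I error.* With one selected model it stayed near nominal. The rise to 0.068 needs selective reporting across models, which the article does not plan.

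**Conclusion.** The concern holds as a point about precision and prespecification. For any rho below 1, and with equal SDs, ANCOVA has the smaller variance: 35% less at rho 0.3, 25% at 0.5, 15% at 0.7 and 10% at 0.8. After the small-sample cost, with 34 completers per arm, the half-width shrinks by between 0.107 SD (0.573 − 0.466, rho 0.3) and 0.013 SD (0.306 − 0.293, rho 0.8). Where in that range the trial falls depends on a correlation that the article does not give.

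The baseline tests carry no information about a randomised comparison and cannot be done for the follow-up-only primary measures. The screening step leaves freedom that is easy to remove. Severity is moderate to minor: no primary conclusion depends on this, but planning the next trial is the stated use of these estimates.

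**What to change.** - Replace item (3) with ANCOVA of the week 6 score on arm and baseline score, with sex and a collapsed race/ethnicity factor as main effects. Fix the collapsing rule before the data are analysed, and use the same covariates for every secondary outcome.
- Base the standardised effect and its 95% CI on this adjusted estimate divided by the baseline SD, and say so.
- Replace the baseline t and chi-square tests with descriptive tables by arm.
- Delete the covariate screening step.

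The cost is a change of wording before the analysis planned for August 2026; every variable is already collected. The downside is a few degrees of freedom, with little or no gain from the stratification terms if they are not prognostic, which is why race/ethnicity must be collapsed to few levels.

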### Assessments and Outcomes

Prospective participants will complete a brief eligibility screening questionnaire in REDCap, which includes basic demographic items (eg, age and sex) and questions aligned with study inclusion/exclusion criteria (eg, “Do you speak English fluently?”). Study assessments will be administered electronically via REDCap at 4 time points: baseline, brief check-in surveys at the end of weeks 2 and 4, and 6-week follow-up. Intervention participants will also be invited to complete an optional postintervention feedback interview via Zoom or telephone.

A description of study measures, including assessment time points, is shown in Table 1. See Figure 2 for the enrollment and intervention schedule.

**Table 1. T1:** Description of survey instruments based on the stress process model [13].

Domain and measure		Time points			
		S^a^	BL^b^	Weeks 2 and 4	FU^c^
Background and context					
Sociodemographic characteristics					
Single-item assessments (age, sex, race/ethnicity, education, geographic location, income, and kinship to care recipient)		✓	—^d^	—	—
Technology proficiency					
Mobile Device Proficiency Questionnaire-16 [51]		—	✓	—	—
Primary stressors: objective					
Functional dependency					
Katz Activities of Daily Living Scale [52,53]		—	✓	—	✓
Lawton-Brody Instrumental Activities of Daily Living Scale [54]		—	✓	—	✓
Caregiver Medical and Nursing Task Inventory [55,56]		—	✓	—	✓
Cognitive impairment					
Revised Memory and Behavior Problems Checklist [57]		—	✓	—	✓
Primary stressors: subjective					
Relational deprivation					
Relational Deprivation Scale [13]		—	✓	—	✓
Secondary stressors: role and intrapsychic strains					
Family conflict					
Family Conflict Scale [13,58]		—	✓	—	✓
Employment conflict					
Job-Caregiving Conflict Scale [13]		—	✓	—	✓
Mood					
Positive and Negative Affect Schedule [59]		—	—	✓	—
Preparedness					
Preparedness for Caregiving Scale [60]		—	✓	—	✓
Cost of care					
Cost of Care Index–Economic Costs Subscale [61]		—	✓	—	✓
Surrogate decision-making					
Advance Care Planning Engagement Survey-9 [62,63]		—	✓	—	✓
Self-care					
Self-Care of Informal Caregivers Inventory [64]		—	✓	—	✓
Role confusion					
Role Captivity Scale		—	✓	—	✓
Predeath grief					
Prolonged Grief Disorder-12 Caregiver Version [65,66]		—	✓	—	✓
Caregiver burden					
Zarit Burden Interview-12 [67]		—	✓	—	✓
Caregiving rewards					
Positive aspects of caregiving [68]		—	✓	—	✓
Mediators					
Caregiver needs					

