Control group activities are designed to match with intervention group activities in terms of interaction frequency and engagement level, minimizing the risk of differential dropout between conditions. All instances of nonadherence or withdrawal, along with reported reasons, will be systematically documented in REDCap to inform feasibility and guide refinements for future trials. While attrition rates of 15% to 30% are common in pilot RCTs and often higher in online interventions [84,85], the study team will monitor retention metrics regularly and, if needed, adjust communication strategies or provide more support to sustain engagement.

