### Harms

Given the minimal-risk nature of the study, adverse events (AEs)—defined as any unfavorable or unintended experience associated with participation, whether related to the study or not—are expected to be rare. Potential risks include mild emotional discomfort when responding to survey or interview questions, exposure to ADRD-related content, or minor frustration when navigating digital platforms. There is also a minimal risk of breach of confidentiality. Participants may skip any questions or activities that feel uncomfortable or distressing. Study staff are trained to recognize and respond to participant distress and will provide appropriate referrals, including to the USC Family Caregiver Support Center, for additional support and resources as needed.

All AEs, serious adverse events (SAEs), and unanticipated problems, as well as any protocol deviations, will be documented using designated reporting forms and logs. The principal investigator (PI) will be notified of any AE or SAE within 24 hours, and all required reporting to the USC IRB, designated Safety Officer, and National Institute on Aging (NIA) Program Officer will be conducted in accordance with institutional and federal policies.

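### Listwise deletion as the only missing-data rule can bias the secondary arm comparisons and leaves the week 2 and 4 scores of later dropouts unused

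*Protocol article*

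**What the plan says.** The Statistical Analysis section lists the efficacy summaries for the secondary outcomes: means by time point, within-group change, between-group difference in change, and standardised effect sizes such as Hedges g with 95% CIs, meant to guide a later efficacy trial. It then states: "Missing data will be handled via listwise deletion". No exception or sensitivity analysis is given, and no baseline-adjusted model is named for the arm comparison.

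Other sections bear on how much will be missing:

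- Retention and Adherence: "attrition rates of 15% to 30% are common in pilot RCTs and often higher in online interventions".
- Harms: "Participants may skip any questions or activities that feel uncomfortable or distressing".
- Study Design and Study Setting: the trial is unblinded and all activities are virtual.
- Assessments and Outcomes: surveys are at "baseline, brief check-in surveys at the end of weeks 2 and 4, and 6-week follow-up". Table 1 places the PHQ-2, GAD-2 and one-item life satisfaction score at weeks 2 and 4. The full PHQ-9, GAD-7 and five-item life satisfaction scale, the Kingston stress scale and the self-efficacy scale are at baseline and week 6 only.
- Sample Size: "A sample size of 40 participants per arm exceeds the upper limit recommended (n=35) for feasibility trials", and this size "allows for adequate precision in estimating key feasibility parameters (recruitment, retention/attrition, and platform usability". No allowance for attrition is stated.

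**The concern.** Under listwise deletion, a participant without the week-6 survey drops out of every change score, and so out of the arm comparison. The comparison is then made among completers. Caregivers know their arm, and the two arms use different platforms, so the people who leave one arm may differ in distress from those who leave the other. Any such difference passes into the estimated effect.

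The data that could correct for this are partly in hand. Baseline scores exist for everyone randomised. Participants who leave after week 2 or week 4 will also have short-form depression, anxiety and life satisfaction scores. The stated rule uses none of this for them.

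What is at stake is the use to which the estimates will be put. The effect sizes are meant to size the next trial, and a required sample size varies with the inverse square of the effect. A modest bias in g therefore becomes a larger error in planning.

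**Working it through.** **Size as stated.** 80 / 2 = 40 per arm, and 40 > 35. The comparison in the Sample Size section is correct for the number enrolled.

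**Week-6 numbers at the cited attrition.** The number with week-6 data per arm is 40 × (1 − d), where d is attrition.

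| d | Per arm | 95% half-width for g |
|---|---|---|
| 0% | 40 | 0.44 |
| 12.5% | 35 | 0.47 |
| 15% | 34 | 0.48 |
| 30% | 28 | 0.53 |

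The half-width is 1.96 × √(2/n + g²/(4n)) with g = 0.28. That is the absolute value of the figure quoted in the Introduction from one review; it is not a design assumption. The break-even attrition is 1 − 35/40 = 12.5%. Treating completion as binomial, the chance that a given arm keeps at least 35 is 43% at 15% attrition and 0.9% at 30%.

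**Bias under deletion, true effect 0.** The documents give no missingness mechanism, so everything here is assumed: 30% loss in the intervention arm, 15% random loss in control, and a baseline to week-6 correlation of 0.5 to 0.6.

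- Intervention loss depends on baseline: the complete-case difference in change is biased by 0.06 to 0.13 SD.
- Intervention loss depends on the week-4 score: the difference in change is biased by 0.02 to 0.05 SD, and complete-case ANCOVA by 0.05 to 0.12 SD.
- Regression imputation by arm from baseline and week-4 scores: bias of 0.005 SD or less.

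A separate simulation under assumptions of the same kind gave complete-case bias of 0.04 to 0.17 SD. Across all of these the range is 0.02 to 0.17 SD.

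**Bias under deletion, true effect −0.28 SD.** Assumed correlation 0.6.

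| Loss mechanism | Change score | ANCOVA |
|---|---|---|
| Completely random, equal | −0.28 | −0.28 |
| Completely random, 30% v 15% | −0.27 | −0.27 |
| Depends on baseline, alike in both arms | −0.28 | −0.28 |
| Depends on baseline, one arm only | −0.20 | −0.28 |
| Depends on interim score, one arm only | −0.33 | −0.36 |

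The −0.27 in the second row is simulation noise around −0.28.

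**Consequence for planning.** Reading −0.20 where the truth is −0.28 multiplies the next trial's size by 0.28² / 0.20² = 1.96. Reading −0.33 multiplies it by 0.28² / 0.33² = 0.72.

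**The case against.** The best defence is that this is a feasibility trial. Efficacy is declared unpowered and preliminary. The biases above are smaller than one standard error of the complete-case estimate, which was 0.224 to 0.257 SD at 40 enrolled per arm in the simulation. Control activities are matched to limit differential dropout. Recruitment and retention rates use screened or enrolled denominators and lose nobody to deletion. All of this stands and bears on severity. It does not make deletion a good rule, because the data for a better one are already being collected.

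A reader might draw several stronger conclusions that the documents do not support.

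- **That deletion will bias the comparison.** It need not. Bias requires loss that depends on scores differently by arm. Where loss depends only on baseline, adjusting for baseline removes it even among completers.
- **That 15% to 30% attrition is this trial's expectation.** The text says only that "attrition rates of 15% to 30% are common in pilot RCTs". The 22 completers of 44 enrolled in the Results section is a count in progress, not an attrition rate.
- **That deletion pushes the trial below 35 per arm, or makes the sample size statement false.** The fall to 34 or 28 is attrition, and no model observes the missing week-6 scores. The 35 is compared with the number enrolled.
- **That skipped items will remove a known share of participants.** Skipping is allowed, but no rate is given. Nor does the article say that one skipped item voids a total, or that scales outside the secondary outcomes enter the efficacy comparison.
- **That better missing-data handling would shrink the standard error by 13% to 17%.** Most of that is baseline adjustment. With complete data the ratio of ANCOVA to change-score SE is √((1 + ρ)/2), which is 0.866 at ρ = 0.5 and 0.894 at ρ = 0.6, so 11% to 13% comes from adjustment alone.

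**Conclusion.** The point holds as a should-fix. Listwise deletion is fixed as the sole rule, and it exposes the between-arm change and Hedges g to bias if dropout is related to baseline or interim scores differently by arm. The size is roughly 0.02 to 0.17 SD under the assumed losses (30% score-dependent in one arm, 15% random in the other). It is about zero if loss is completely random or depends on baseline alike in both arms. The documents do not show which mechanism will operate.

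The rule also leaves interim data unused for depression, anxiety and life satisfaction. For stress and self-efficacy, which have no interim form, the gain from a better method is smaller and comes mainly from baseline adjustment and auxiliary variables. No method proposed here protects against loss that depends on the unseen week-6 values themselves.

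The sample size point is separate and is a matter of attrition. At 15% to 30%, about 34 to 28 per arm would supply week-6 measures. These include usability, which the Sample Size section names as a parameter to be estimated precisely and which Table 1 places only at week 6.

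**What to change.** Replace the sentence in the Statistical Analysis section with wording to this effect: all randomised participants are analysed in the arm to which they were assigned; secondary outcomes are compared with a baseline-adjusted likelihood-based model or with multiple imputation by arm; auxiliary variables are baseline scores, log-in counts (tracked on both platforms) and, for depression, anxiety and life satisfaction, the week 2 and 4 short forms; scale totals are prorated when most items are answered; listwise deletion is reported as a sensitivity analysis.

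In the Sample Size section, keep the statement that 40 enrolled exceeds 35. Add that at the 15% to 30% attrition cited later in the article, about 34 to 28 per arm would provide week-6 measures, including usability, while recruitment and retention rates are unaffected.

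The cost is a change of wording and slightly more analysis work. No new data are needed, and analysis is planned for August 2026. The stated size for week-6 measures will look less favourable.

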#### Exploratory Objective

The exploratory objective is to generate preliminary effect size estimates to inform sample size calculations for a future fully powered RCT.

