### Limitations

Several limitations warrant consideration. Given that the primary objective of this pilot study is to evaluate feasibility and acceptability, the sample is not statistically powered to examine efficacy for improving caregiver outcomes. Eligibility criteria require participants to have device/internet access, which, in addition to the study’s virtual modes of recruitment, may yield a sample with higher digital literacy than the broader caregiving population. Self-selection bias may also impact generalizability, as individuals who choose to participate may be more motivated, more receptive to digital caregiving tools, or differ in caregiving stress levels, which can bias estimates of feasibility and acceptability. Finally, the relatively short intervention period limits the ability to evaluate sustained engagement, longer-term acceptability, and barriers or facilitators influencing CarePair uptake over time.

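### A trial stated to be unpowered for outcomes applies a .05 significance rule to all analyses and counts within-arm change as evidence of preliminary efficacy

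*Protocol article*

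**What the plan says.** Under Sample Size, the protocol article states that "the study is not powered to detect clinically meaningful differences in outcomes" and appeals to guidance that "prioritizes the estimation of feasibility parameters over formal hypothesis testing or power-based sample size calculations". Limitations repeats that "the sample is not statistically powered to examine efficacy for improving caregiver outcomes". The number per arm is justified by a rule of thumb: "A sample size of 40 participants per arm exceeds the upper limit recommended (n=35) for feasibility trials".

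Statistical Analysis then sets one rule for everything: a P "value of .05 will be used to indicate significance in all analyses". The same paragraph introduces four items as the examination of preliminary efficacy in the secondary outcomes. The second is "2) within-group change from baseline to follow-up"; the third is the between-group difference in change; the fourth is a standardized effect size such as Hedges g with a 95% CI, meant to guide planning of a later trial. Missing data are handled by listwise deletion. No test is named for the within-group item, but a rule for all analyses leaves it no exemption.

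The Exploratory Objective is to "generate preliminary effect size estimates to inform sample size calculations for a future fully powered RCT". No important difference or other external basis for that later sample size is named.

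**The concern.** The two parts of the article pull in different directions. One says that the trial cannot support conclusions about outcomes and that estimation comes first. The other provides a threshold for calling those outcomes significant.

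The within-arm item is the weaker part. Study Design says that the trial is unblinded, and the secondary outcomes are self-reported scales. Change within the CarePair arm therefore carries time trends, regression to the mean and expectation as well as any effect of the app. Control participants read most of the same articles, so they may well improve too. A significant change in one arm beside a non-significant change in the other is easily read as an effect, and no comparison of the arms has been made.

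For the between-arm comparison, low power means that a non-significant result is uninformative, and an estimate that does cross .05 is likely to be too large. These estimates are then to inform planning of the next trial.

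**Working it through.** **Inputs.** 40 per arm (Sample Size). Retention and Adherence cites 15% to 30% attrition as common, so listwise deletion could leave 40 × 0.85 = 34 or 40 × 0.70 = 28 per arm. Alpha is .05, taken as two-sided to match the 95% CIs. The article gives no target effect, SD or baseline-follow-up correlation r, so these are assumptions and ranges are shown. The illustrative effect is 0.28 SD, the only effect size in the article (Technology to Bolster Caregiving Support). Its meaning there is unclear: it may be a pooled effect for mobile apps or a contrast with web-based programs. Effects are in baseline-SD units, with equal SDs at both times.

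**The plan's own figure.** There is no power formula to reproduce. The target is 40 > 35 by rule of thumb, and 2 × 40 = 80.

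**Within-arm change with no CarePair effect.** Let both arms improve by the same Δ. The SD of change is √(2(1−r)). The one-sample t test has noncentrality Δ√n / √(2(1−r)), which gives the probability p of a significant improvement. The chance that exactly one arm is significant is 2p(1−p).

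| n per arm | r | Δ | Noncentrality | p | Exactly one arm |
|---|---|---|---|---|---|
| 40 | 0.5 | 0.2 | 1.27 | 0.23 | 36% |
| 40 | 0.5 | 0.3 | 1.90 | 0.46 | 50% |
| 40 | 0.7 | 0.4 | 3.27 | 0.89 | 20% |
| 28 | 0.5 | 0.2 | 1.06 | 0.17 | 29% |
| 28 | 0.7 | 0.3 | 2.05 | 0.51 | 50% |

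Over Δ 0.2 to 0.4, r 0.5 to 0.7 and n 28 to 40, the range is about 20% to 50% (17% to 50% with a normal approximation). By symmetry, in half of these cases the significant arm is CarePair alone.

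**Between-arm change score, true effect 0.28, 40 per arm.** SE = √(2(1−r)) × √(2/40). The smallest significant difference is c = 1.99 × SE. With a = (c − 0.28)/SE, the mean significant estimate in the favourable direction is 0.28 + SE × φ(a)/(1−Φ(a)).

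| r | SE | Power | c | Mean if significant | Ratio to 0.28 |
|---|---|---|---|---|---|
| 0.3 | 0.265 | 18% | 0.53 | 0.67 | 2.4 |
| 0.5 | 0.224 | 24% | 0.45 | 0.58 | 2.1 |
| 0.7 | 0.173 | 36% | 0.35 | 0.46 | 1.7 |

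At r = 0.5, power falls to 21% at 34 per arm and 18% at 28. With an assumed 0.5 SD effect and r = 0.5, it is 61%, 54% and 46% at 40, 34 and 28 per arm.

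**Change score against baseline adjustment, 40 per arm.** The 95% CI half-width is 1.96 × √(2(1−r)) × √(2/40) for the change score and 1.96 × √(1−r²) × √(2/40) after adjustment. At r = 0.5 this is 0.44 against 0.38 SD; at r = 0.7, 0.34 against 0.31 SD.

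**What an observed g can tell the next trial.** At g = 0.28 and 40 per arm, SE = √(2/40 + 0.28²/160) = 0.225. The unadjusted CI is 0.28 ± 0.44, or −0.16 to 0.72. With n per arm = 2 × ((1.96 + 0.842)/d)² for 80% power, d = 0.72 needs 31 and d = 0.28 needs 201. At or below zero there is no sample size.

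**The case against.** The strongest reply is that this is a feasibility pilot that discloses its limits. The primary objective and the progression criteria concern feasibility and acceptability, and lack of power is stated twice. The guidance cited under Sample Size gives priority to estimation; it does not forbid tests. Within-group change is listed beside between-group differences and CIs. All of that is fair. It makes this a tension to be removed by wording, and it confines the harm to the efficacy reading and later planning. It does not exempt the efficacy outcomes from a rule written for all analyses.

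Four stronger readings are tempting, and the documents do not support them.

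- A reader might infer that the observed g will set the size of the next trial. The article says only that effect sizes will inform or guide planning, and Sample Size and Statistical Analysis attach CIs to them.
- A reader might count every scale measured at baseline and follow-up as an efficacy test. Statistical Analysis limits the efficacy items to secondary outcomes: four in the objective, five in Table 1, six in the text. Six independent tests would give 1 − 0.95⁶ = 26.5% for at least one false positive, or about 16% to 21% if the outcomes correlate at an assumed 0.5 to 0.7. How multiplicity is handled may also sit in an analysis plan that is not shown.
- A reader might take 0.45 SD as a fixed bar for significance at 40 per arm. For change scores that holds only at r = 0.5.
- A reader might treat 0.28 as the expected effect here. The article does not tie it to a control that reads most of the same articles.

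**Conclusion.** The point holds as a wording fault in stated text, and it should be corrected. The .05 rule covers outcomes for which the trial is declared unpowered, and within-arm change is offered as evidence of efficacy that it cannot supply.

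With equal improvement in both arms and no CarePair effect, a split verdict between arms arises in about 20% to 50% of trials for each outcome, under the assumed improvement, correlation and completer numbers. Power of about 18% to 36% at 40 per arm, with exaggeration of roughly 1.7 to 2.4 times among significant results, is illustrative because it depends on 0.28 SD and on the correlation. The qualitative conclusion does not depend on 0.28: at 0.5 SD and r = 0.5, power is still only 46% to 61%. An observed g of 0.28 would be too imprecise to fix a later sample size. The feasibility conclusions are not affected.

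**What to change.** In Statistical Analysis:

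- limit the .05 rule so that it does not apply to the efficacy outcomes;
- name the baseline-adjusted between-arm difference with its 95% CI, for each named secondary outcome, as the efficacy estimate;
- present within-arm change descriptively, without tests.

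In the Exploratory Objective and Statistical Analysis, add that the next trial's sample size will rest on an important difference together with this pilot's SD, baseline-follow-up correlation and attrition, and that g and its CI are supporting information only.

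The change is to wording and analysis code, with no new data, visits or participants. Analysis is planned for August 2026, so it can be made beforehand. Baseline adjustment also narrows the CI at no cost. The one real loss is that the sponsor can no longer claim a significant pilot result.
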